# **8. Adverse Events**

8. 1. Definition

8. 1. 1. Definition of adverse events

“Any unfavorable or unintended sign, symptom or disease occurring in subjects in association with the use of an investigational medicinal product and which does not necessarily have a causal relationship with the investigational drug. ”

In particular, any abnormal laboratory finding or sign which leads to treatment discontinuation is to be considered as an adverse event.

8. 1. 2. Definition of serious adverse events

A serious adverse event is any untoward medical occurrence or adverse drug reaction that at any dose of an investigational drug:

- results in death or is life-threatening;
- requires hospitalization or prolongation of existing hospitalization
- causes a persistent or significant disability or incapacity.
- results in a congenital anomaly or birth defect; or
- is associated with any other medically important condition. .

8. 2. Procedures

8. 2. 1. Notification and documentation of adverse events

Any adverse event should be documented on the patient chart and reported on the case report form (CRF).

8. 2. 2. Notification and documentation of serious adverse events

If any serious adverse event is found during the study (V0 to V2), the investigator must report the occurrence of such event immediately or **within one working day** to Astellas Korea by phone or fax, using Astellas’ standard SAE report form.

- In any case, the report must show the identity of the investigator and be dated and signed. It should also give an assessment of the causal relationship between the event and the study drug.

8. 2. 3. Procedures during and after the study

The investigator should follow up and monitor patients for the outcome of clinical adverse events or abnormal laboratory findings until recovery or stabilization of their condition.

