# **3. Description of the Study**

This study is an open-label, multi-center, observational, comparative trial conducted for three months by nine urologists in South Korea.

This study is also a non-inferiority study hypothesizing that the effect of solifenacin is not inferior in patients with frequency only to others with both frequency and urgency.

Principal investigator: [name], University of Ulsan Asan Medical Center

Co-investigator: [name] [name], Inha University Hospital

Co-investigator: [name] [name] (co-investigator), Keimyung University Dongsan Medical Center

Co-investigator: [name] [name], Korea University Hospital

Co-investigator: [name] [name], Pusan National University Hospital

Co-investigator: [name] [name], Daegu Catholic University Hospital

Co-investigator: [name], Samsung Medical Center, Sungkyunkwan University

Co-investigator: [name], Chungnam National University Hospital

Co-investigator: [name] [name], Chonnam National University Hospital

In this study, the screening period is from week 0 to week 3. Patients included in the trial will receive one tablet of solifenacin succinate (5 mg or 10 mg) for a period of three months.

This study will involve four planned visits: pre-inclusion visit (V0), inclusion visit (V1), 1 intermediate visit (V2, 4-week intervals) and end-of-study visit (V3, week 12).

If needed, visits may take place within 7 days before or after the theoretical dates calculated from V1.

Demographics include body weight, age, sex, education level, occupation and parity (for female only). Patients are asked to keep a 3-day voiding diary at baseline and at weeks 4 and 12 after initiation of treatment.

Patients are divided into two groups: group 1 (frequency without urgency) and group 2 (frequency with urgency). Both of the groups receive solifenacin succinate over a period of 12 weeks.

- At the beginning, patients receive solifenacin succinate 5 mg.

- At week 4, they can have the dose escalated to 10 mg after consultation with the investigator.

- If there are patients who are not able to withstand the new dose after dose escalation, it can be reduced back.

Uroflowmetry and residual urine measurement will be performed at baseline and week 12.

Patients will be asked to complete the PPBC and OABSS questionnaires at baseline and at weeks 4 and 12 of treatment. At the end of the study, they will be asked to complete the BSW questionnaire.

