# **7. Practical Conduct of the Study**

7. 1.Visit 0 (days -21 to 0)

- An oral explanation of the clinical trial to subjects.
- Dating and signing of the informed consent form by subjects
- Collection of necessary information including demographics, disease history, clinical history and associated conditions and relevant concomitant medications.
- Physical examinations including a digital rectal exam in male subjects.
- Laboratory tests: Urinalysis, CBC, chemistry and serum PSA (only in male subjects)
- PPBC and OABSS assessments
- Uroflowmetry and residual urine assessment
- A voiding diary is explained and given to each subject.
- Identification of concomitant medications

7. 2.Visit 1 (day 0)

- Laboratory test results are confirmed.
- Subjects for the clinical trial are selected based on the inclusion and exclusion criteria after an evaluation of their voiding diaries.
- Subjects are prescribed one Vesicare 5 mg tablet to take before sleep for four weeks. The tablet should not be chewed, divided or crushed.
- Concomitant medications are identified.
- The voiding diary is given to each subject.

7. 3. Visit 2 (week 4)

Visit 2 will take place four weeks after the inclusion visit (or if necessary, within seven days before or after the theoretical date).

- Adverse events are identified.
- The date when each subject took the study drug is confirmed.
- The voiding diary is evaluated.
- The PPBC and OABSS questionnaires are evaluated.
- Subjects are prescribed one 5 or 10mg Vesicare 5 mg or 10 mg tablet to take before sleep for eight weeks. The tablet should not be chewed, divided or crushed. Dose escalation to 10 mg is determined after consultation between the investigator and subjects.
- Concomitant medications are identified.
- The voiding diary is given to each subject.

7. 4. Visit 3 (week 12)

Visit 3 will take place eight weeks after the inclusion visit (or if necessary, within seven days before or after the theoretical date).

- Adverse events are identified.
- The date when each subject took the study drug is confirmed.
- The voiding diary is evaluated.
- The PPBC and OABSS questionnaires are evaluated.
- Concomitant medications are identified.
- Uroflowmetry and residual urine assessment
- Patient satisfaction with the study drug is assessed by the BSW questionnaire.

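### Section 8.2.2 ends the serious adverse event reporting window at V2 (week 4), although the study and treatment run to V3 (week 12)

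*Protocol*

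**What the plan says.** Protocol section 8.2.2 sets the only expedited reporting rule: "If any serious adverse event is found during the study (V0 to V2), the investigator must report the occurrence of such event immediately". The outer limit is one working day, and the report goes to the sponsor on its standard form, signed and dated, with an assessment of causality.

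The protocol describes the study period differently elsewhere:

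- Section 3 lists four visits, V0 to V3. After the pre-inclusion and inclusion visits come "1 intermediate visit (V2, 4-week intervals) and end-of-study visit (V3, week 12"). The Study Schedule agrees: V2 at week 4 and V3 at week 12, each plus or minus 7 days.
- Section 3 on treatment: "Both of the groups receive solifenacin succinate over a period of 12 weeks".
- Section 7.2 on the first prescription, at V1: "Subjects are prescribed one Vesicare 5 mg tablet to take before sleep for four weeks".
- Section 7.3 on V2: "Visit 2 will take place four weeks after the inclusion visit". The prescription issued there is a 5 mg or 10 mg "tablet to take before sleep for eight weeks".
- Section 3 on the higher dose: "At week 4, they can have the dose escalated to 10 mg after consultation with the investigator".

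**The concern.** Section 8.2.2 treats V0 to V2 as the whole study, but V2 is the intermediate visit. The stated window closes at the visit where the longer of the two prescriptions is issued and where 10 mg first becomes possible.

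A site that applied the parenthesis as written could hold a serious event found at, say, week 8 until routine CRF collection and still be following the protocol. The sponsor would learn of it late, without the form and causality assessment that 8.2.2 requires. Adverse events are a listed safety endpoint, and nine centres have to apply this sentence in the same way.

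**Working it through.** The protocol states no figure for this point, so there is none to reproduce. The check compares the timeline with the reporting window and then asks whether any other section closes the gap.

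**Treatment time outside the window.** Inputs: V2 at week 4 and V3 at week 12, each plus or minus 1 week (Study Schedule; sections 3 and 7.3). Dosing starts at V1, day 0.

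Weeks outside = V3 − V2; share = (V3 − V2) / V3.

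| Case | V2 (week) | V3 (week) | Weeks outside | Share |
| --- | --- | --- | --- | --- |
| Nominal | 4 | 12 | 8 | 8/12 = 66.7% |
| Latest V2, earliest V3 | 5 | 11 | 6 | 6/11 = 54.5% |
| Earliest V2, latest V3 | 3 | 13 | 10 | 10/13 = 76.9% |
| V3 as dated in the text of section 7.4 | 4 | 8 | 4 | 4/8 = 50.0% |

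The last row is needed because section 7.4 is headed week 12 but its text dates Visit 3 to eight weeks from inclusion. On either dating, at least half of the time from V1 to V3 falls after V2 on the nominal schedule.

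**10 mg exposure outside the window.** Sections 3 and 7.2 fix 5 mg from V1 to V2, and sections 3 and 7.3 allow 10 mg only from V2. Planned 10 mg exposure before V2 is therefore zero, and all of it lies outside the window. The general posology line in section 5.1, which names both strengths, does not open 10 mg any earlier.

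**Does another section extend the duty to V3?**

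- Section 8.2.1 requires every adverse event on the chart and CRF, with no visit limit. It sets no deadline and no direct notice to the sponsor.
- Section 8.2.3 covers follow-up of the outcome, not notification.
- Section 7.4 and the Study Schedule have adverse events identified at V3, and section 6.3 asks about the time since the last visit. Events between V2 and V3 are therefore collected, but no expedited duty is attached to them.
- Section 9.2 refers serious events that cause drop-out to section 8.2 and adds no visit limit of its own. The section it points to contains the V0 to V2 limit, so it covers later drop-outs only on a generous reading. It does not reach serious events in patients who stay in the study.
- Section 11.3 has the ethics committee told of events bearing on patient safety. That is a different recipient.

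No section expressly extends sponsor notification to V3.

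**The case against.** The strongest reply is that the main clause speaks of the study as a whole and the parenthesis is a slip in visit numbering. Section 7.4 contains another timing slip, and nothing suggests that a four-week window was chosen. On that view the text is contradictory and does not clearly exclude later events, and a sensible site would report throughout. This is probably right about intent, and it is why the point is classed as an internal contradiction and not as a design decision. It does not remove the defect: the parenthesis is the only place where the window is defined, and a literal reading of it stops at week 4.

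A reader might go further and infer that serious event data after week 4 would be missing. The documents do not support that. Sections 8.2.1, 7.4 and 8.2.3 keep recording, identification at V3 and follow-up in force without a V2 limit, and section 10.3 analyses adverse events in everyone who took the drug at least once. What is at risk is the speed and form of notification.

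It is also fair to say that 67% is a share of calendar time. The protocol gives no serious event rate, so the figure does not count missed reports.

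**Conclusion.** The point stands as an internal contradiction that is wrong as written. Read literally, section 8.2.2 ends one-working-day sponsor notification at week 4 of a 12-week treatment period. Nominally 8 of 12 treatment weeks (67%; 55% to 77% across the visit windows) and all planned 10 mg exposure lie outside it. The consequence is delayed or absent expedited notification, chiefly for serious events that do not lead to drop-out; it is not lost data.

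The size rests on the week 12 date for V3 given in section 3 and the Study Schedule; on the date in the text of section 7.4 the share is 50%. The sample size, margin and primary analysis are untouched. The correction is still needed, because the rule concerns safety oversight and the stated window misses most of the treatment period.

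**What to change.** In section 8.2.2, replace (V0 to V2) with (V0 to V3, end-of-study visit), or delete the parenthesis so that the duty covers the whole study.

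In the same amendment, reconcile the Visit 3 timing in the text of section 7.4 with that section's week 12 heading. Until then a window ending at V3 has an ambiguous end: with V3 at week 8 and treatment to week 12, it would still leave 12 − 8 = 4 treatment weeks uncovered. It would also help to state in section 9.2 that its reference to section 8.2 applies at any time during the study.

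The cost is a few words in a protocol amendment and a note to the nine centres. No change to the design, data collection or analysis is needed.

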# **9. Drop-out**

9. 1. Reasons for drop-out

Patients may drop out of the study at any time, for whatever reason, once they decide to do so, or the investigator may decide to withdraw patients from the study. All dropouts must be documented and the investigator must specify the reasons (e.g., failure of a patient to pay a visit despite receipt of notice, lack of cooperation from the patient, lack of treatment efficacy, worsening of the clinical condition obstructing continued compliance with the protocol, occurrence of adverse events ...).

9. 2. Procedures

- All dropouts must be recorded on the patient chart and CRF.
- If any event causing a drop-out meets the definition of serious adverse events, the investigator will carry out the procedures as described in section 8.2.
- For patients lost to follow-up, the CRF must be completed until the date the last visit took place. The investigator will use his/her best effort to find out the reason why a patient failed to pay the visit, if any, and to determine the state of his/her health.

**Power analysis of a non-inferiority test for the difference between two means**

**Numeric results for a non-inferiority test (H0: D <= -|E|; H1: D > -|E|)**

**Test statistic: T-test**

**Equivalence Margin / Actual Difference / Significance / Standard Deviation 1 / Standard Deviation 2**

**Power N1/N2 (E) (D) (Alpha) Beta (SD1) (SD2)**

0.80085  325/325 -0.50 0.00 0.05000 0.19915 2.56 2.56

0.80034  226/226 -0.60 0.00 0.05000 0.19966 2.56 2.56

0.80197 167/167 -0.70 0.00 0.05000 0.19803 2.56 2.56

0.80191 128/128 -0.80 0.00 0.05000 0.19809 2.56 2.56

0.80095 101/101 -0.90 0.00 0.05000 0.19905 2.56 2.56

0.80120  82/82 -1.00 0.00  0.05000 0.19880 2.56 2.56

**References**

Julious, Steven A. 2004. 'Tutorial in Biostatistics. Sample sizes for clinical trials with Normal data.'

Statistics in Medicine, 23:1921-1986.

10. 2. Handling of missing, unused or inconsistent data

In the analyses, for patients who are prematurely withdrawn, the last observation carried forward (LOCF) method will be used: This means that the results of the last post-baseline available assessment (Vend) will be analyzed (or that the baseline values will not be carried forward).

Missing data will be made available in the data management report.

The decision to replace missing items will be made prior to the end of the study.

10.3. General principles of outcome analysis

The analysis of data obtained from study subjects will be conducted by three main analysis approaches: intention to treat (ITT), full data analysis set (FAS) and per protocol (PP).

The ITT analysis includes all data obtained from subjects who have ever received the investigational drug at least once. This approach is used to analyze safety data related to adverse events.

The FAS analysis set is a group of subjects who have had the primary efficacy endpoint measured at least once since administration of the investigational drug, and all the measurement data is included in the analysis. However, the analysis excludes patients who have failed to meet the inclusion criteria or have taken any of prohibited concomitant drugs. In case missing data occurs at any point of time or if there are any subjects who drop out before the end of the study, data analysis is conducted for conservative assessment as if the latest data were obtained at such point of time (last observation carried forward).

The PP analysis includes data obtained from patients treated in compliance with the study protocol among those subjects included in the ITT analysis.

Efficacy data are analyzed primarily by the FAS approach and secondarily by the PP approach. The analysis of adverse event data is performed on an ITT basis, and laboratory test data are analyzed using an FAS (data itself) approach. The findings of those analyses are compared, but if any significant differences are found, the results of each analysis should be described.

10. 4. Statistical analysis methods

10.4.1. Demographics and medical history

Data from all the subjects who participate in this clinical study will be evaluated on a group-by-group basis. We will calculate the mean, standard deviation (SD), maximum and minimum values for continuous data and the absolute and relative frequencies for categorical data. Demographics and baseline data will be compared between two groups. Continuous variables are compared between groups and study centers by the t-test, Mann-Whitney test or ANOVA test and Kruskal-Wallis test, while categorical variables are compared by the Chi-square test and using the Mantel-Haenszel test at each center as a stratification factor. If any significant difference between two groups is accepted, the efficacy analysis will use the difference as a correct factor to correct heterogeneity between the groups.

10.4.2. Primary efficacy assessment

A t-test will be used to compare changes in frequency of urination (from baseline to the end of the study) between study groups on the voiding diary (see Annex 1) and calculate a 95% confidence interval for the difference between the groups. Further analysis, if necessary, will be conducted with a generalized linear model in order to correct heterogeneity between the groups.

10.4.2. Secondary efficacy assessment

Secondary efficacy endpoints (i.e., PPBC, OABSS and BSW) will be analyzed using the the Wilcoxon signed-rank sum test or paired t-test for continuous data and the McNemar test for categorical data. If necessary, a mixed effect model or generalized estimation equation will be used as an analysis tool to test the difference between study groups.

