# **2. Study Objectives**

To examine the effects of solifenacin succinate treatment in patients who have frequent micturition with or without urgency.

2. 1. Primary objective

To compare changes in micturition frequency on 3-day voiding diary from baseline to week 12 of treatment with solifenacin succinate between group 1 (frequency without urgency) and group 2 (frequency with urgency)

2. 2. Secondary objectives

- To compare improvements in the PPBC at week 12 of treatment with solifenacin succinate.

- To compare improvements in the OABSS at week 12 of treatment with solifenacin succinate.

- To compare percent changes in mean void volume at week 12 of treatment with solifenacin succinate.

- To compare percent changes in maximum bladder capacity at week 12 of treatment with solifenacin succinate.

- To assess patient satisfaction by the BSW questionnaire at week 12 of treatment with solifenacin succinate.

- To identify pre-treatment factors (age, sex, baseline episodes of frequency, education level, etc) associated with frequency improvement in group 1.

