# **6. Evaluation of the Study Drug**

All efficacy endpoints, except the BSW questionnaire, are compared with baseline.

6. 1. Primary efficacy endpoint

- Changes in micturition frequency on the voiding diary (Appendix 1) (from baseline to end of study)

6. 2. Secondary efficacy endpoints

- PPBC (changes from baseline to week 12)
- OABSS (changes from baseline to week 12)
- BSW questionnaire at week 12

6. 3. Safety endpoints

General clinical safety will be assessed based on data on spontaneously reported adverse events at each visit. To this end, subjects will be asked: “Since last visit*,* have you had any unusual symptoms or any health problems you had never experienced before?”

- Adverse events
- Changes in maximum flow rate (MFR) measured by uroflowmetry (from baseline to week 12)
- Changes in post-void residual (PVR) urine volume assessed by bladder scan (from baseline to week 12)

According to the recommendations of the International Consultation on BPH, the PSA will be measured at baseline. Normal laboratory ranges will be provided in the CRF.

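### Section 10.4.2 assigns paired tests to the secondary endpoints: they do not answer the comparative PPBC and OABSS objectives and cannot be computed on BSW, which is measured once

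*Protocol*

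**What the plan says.** **Methods.** Section 10.4.2 (Secondary efficacy assessment) opens: "Secondary efficacy endpoints (i.e., PPBC, OABSS and BSW) will be analyzed using the" and then names the "Wilcoxon signed-rank sum test or paired t-test for continuous data and the McNemar test for categorical data". It continues: "If necessary, a mixed effect model or generalized estimation equation will be used as an analysis tool to test the difference between study groups". The statistical analysis row of the synopsis says the same.

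**Objectives.** Section 2.2 includes "To compare improvements in the PPBC at week 12 of treatment with solifenacin succinate" and "To compare improvements in the OABSS at week 12 of treatment with solifenacin succinate". For BSW the verb differs: "To assess patient satisfaction by the BSW questionnaire at week 12 of treatment with solifenacin succinate". Section 2.2 also lists percent change in mean void volume and in maximum bladder capacity.

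**Measurement.** PPBC and OABSS are completed at baseline, week 4 and week 12 (Section 3 and Study Schedule). For BSW, Section 3 says: "At the end of the study, they will be asked to complete the BSW questionnaire". The Study Schedule marks it at V3 only, and Section 6 says: "All efficacy endpoints, except the BSW questionnaire, are compared with baseline".

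**Contrast.** The primary endpoint, in the other section numbered 10.4.2, has a committed t-test between groups on change, with a 95% confidence interval.

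**The concern.** The named tests compare a patient with himself or herself. They can show that PPBC or OABSS moved from baseline in a group, but not whether one group improved more than the other. The question that the secondary objectives appear to ask therefore has no committed analysis. The method that would answer it is left to a judgement of need, with no criterion, in an open-label trial where that judgement could be made after the data are seen.

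For BSW the problem is more basic: the analysis as written cannot be carried out. A later analysis plan would either inherit an instruction that cannot be executed or depart from the protocol.

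**Working it through.** **1. The plan's own figure.** The protocol states no figure for the secondary endpoints. Its only design figure is 128 per group for the primary test (Section 10.1: margin 0.80, SD 2.56, alpha 0.05, true difference 0). The standard error is 2.56 × √(2/128) = 0.32, and 0.80/0.32 = 2.5. With a one-sided 5% critical value, approximate power is Φ(2.5 − 1.645) = Φ(0.855) = 0.804. The exact noncentral-t value is 0.8019, against 0.80191 stated. The figure reproduces. It has no bearing on this point except to supply the group size used in step 4.

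**2. Tests against design.**

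| Endpoint | Measured | Objective (2.2) | Paired tests computable? | Do they answer the objective? |
|---|---|---|---|---|
| PPBC | Baseline, weeks 4 and 12 | Compare improvements | Yes, within each group | No |
| OABSS | Baseline, weeks 4 and 12 | Compare improvements | Yes, within each group | No |
| BSW | Week 12 only | Assess satisfaction | No | No |

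Sections 3 and 4.3 allocate each patient to one group by urgency on the diary, with no matching. No patient in group 1 is linked to one in group 2, so the only available pairing is within a patient over time.

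**3. BSW.** Section 10.4.2 includes it by name. Sections 3 and 6 and the Study Schedule give it one measurement and no baseline. No before-and-after pair exists for any patient, so neither the signed-rank test, the paired t-test nor McNemar's test can be formed. This needs no assumption.

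**4. What paired results reveal about the group difference.** This is an illustration with assumed values: 128 per group, SD of change 1.0, two-sided 5%, 4,000 simulated trials.

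| Assumed mean change, group 1 / group 2 | Both paired t-tests significant | Two-sample t-test significant |
|---|---|---|
| −1.0 / −1.0 | 100% | 5.2% |
| −0.5 / −1.0 | 100% | 97.8% |

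The arithmetic agrees. Within a group, the expected test statistic is 0.5 × √128 = 5.66 or 1.0 × √128 = 11.3 in size, both far beyond the critical value. Between groups, in the second row, it is 0.5/√(2/128) = 0.5/0.125 = 4.0, so power is about Φ(4.0 − 1.96) = 0.979. The paired pattern is identical in the two rows although the group difference is nil in one and twofold in the other.

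**5. Where unpaired methods appear.** Section 10.4.1 names the t-test, Mann-Whitney, chi-square and Mantel-Haenszel tests, but for demographics and baseline data. The primary endpoint has its between-group t-test. For the secondary endpoints only the conditional model remains.

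**6. Lists against objectives.** Percent change in mean void volume and in maximum bladder capacity are in Section 2.2, but not in the endpoint list of Section 6.2 nor in the three-item list of Section 10.4.2.

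**The case against.** *A between-group method is named.* This is true, and it rules out a stronger reading that a reader might infer: that the protocol has no such method, or that the trial must end without a group estimate for PPBC and OABSS. The mixed model or GEE could supply one. What stands is that it is conditional, with no trigger, while the paired tests are unconditional. Model detail may properly sit in an analysis plan; the conditional status is set by the protocol itself.

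*The objectives may mean comparison with baseline.* Only the primary objective names both groups, and Section 6 speaks of comparison with baseline, which paired tests fit. The wording is ambiguous. But an improvement is already a change from baseline, so comparing improvements needs a second group; the study is described as comparative with a between-group hypothesis; and the conditional sentence in 10.4.2 itself aims at the difference between groups.

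*A rank-sum test may have been intended.* The test's name in 10.4.2 blends the paired signed-rank and the unpaired rank-sum tests. Next to a paired t-test and McNemar's test, the paired reading is the natural one; at best this is another reason to reword.

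*BSW needs no group comparison.* That stands. The objective is only to assess satisfaction, so the protocol cannot be faulted for lacking a BSW comparison. The fault is that the assigned tests are impossible.

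*How often would readers be misled?* One might infer a frequency with which one group is significant and the other is not despite equal effects. With within-group power p this is 2p(1 − p). At 128 per group it runs from 47% when the true change is 0.2 SD (p = 0.61) to 0.03% when it is 0.5 SD (p = 0.9999). The protocol gives no effect size for these endpoints and does not plan to draw group conclusions that way, so no single figure is supported.

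**Conclusion.** The point holds within these limits. For PPBC and OABSS, the committed tests describe change within a group, and the only between-group analysis is optional with no stated trigger. This rests on reading the objectives to compare improvements as between-group, which the design supports though the wording does not spell it out. For BSW, the assigned tests cannot be computed for any patient; that is a plain contradiction within the protocol and rests on no assumption.

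The simulated percentages show the logic under assumed values and are not estimates for this trial. The effect is confined to secondary endpoints.

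The absence of void volume and bladder capacity from the endpoint and analysis lists is a separate mismatch between objectives and endpoints. It does not depend on the argument about paired tests.

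**What to change.** Reword Section 10.4.2 (Secondary efficacy assessment) and the matching synopsis row:

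- **PPBC and OABSS:** make the between-group comparison of change to week 12 the committed analysis, with a 95% confidence interval. Either a two-sample t-test or Mann-Whitney test on change, in line with the primary analysis, or the mixed model or GEE already named with its condition removed, would do.
- **Paired tests:** keep them as within-group description of PPBC and OABSS.
- **BSW:** report week-12 proportions per group. If the groups are to be compared, use an unpaired test: chi-square, or Mantel-Haenszel stratified by centre.
- **Baseline-score adjustment:** optional. The groups are not randomised but are defined by baseline urgency, so adjusting for the baseline score can answer a different question from comparing raw changes (Lord's paradox). It is not needed to cure this defect.

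Separately, reconcile Section 2.2 with Sections 6.2 and 10.4.2 on percent change in mean void volume and in maximum bladder capacity.

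The cost is wording in Sections 10.4.2 and 6.2 and the synopsis. No new data are needed, and the sample size and primary analysis do not change.
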